##### Study population

In order to be eligible for inclusion the following criteria were used:Willing and able to make use of a smartphone and to give informed consent for participation in the studyAdults ≥18 years oldIschemic or non-ischemic HF diseaseFunctional New York Heart Association (NYHA) class 2–3Reduced left ventricular ejection fraction ≤40%Ambulatory HF patients in stable condition: at least one hospitalization due to HF, but no hospitalization during the month before start of the trial and no planned surgeryGood cognitive function, if cognitive impairment is suspected, the patient will be evaluated with Mini Mental State Examination (MMSE)Sufficient knowledge of the native language (Dutch in Belgium, Italian in Italy)

HF patients who fulfil the above mentioned criteria are excluded if:They suffer from a concomitant end-stage chronic kidney disease necessitating haemodialysisThey are already participating in a disease management program influencing the HeartMan intervention

##### Investigation procedure

A general overview of this study is presented in Fig. 1 and described in detail in following paragraphs.

**Fig. 1 Fig1:**
[figure not shown]
Study flow chart

##### Recruitment and enrolment

Patient recruitment is organized across three Belgian and one Italian hospital, representing one geographic area in each country. The participating hospitals in Belgium include one university hospital (University Hospital Ghent) and two local hospitals (AZ Maria Middelares Ghent and OLV Hospital Aalst). In Italy, one local hospital (Rieti General Hospital) as well as the local health authority (ASL Rieti) with their general physicians is involved.

The target population screened for participation are stable ambulatory HF patients who visit their treating cardiologist on a regular basis. At the time of consultation, the physician or HF nurse identifies eligible patients, briefly presents the study and asks about their interest in participation. If the patient shows interest, he is asked to come back for a scheduled appointment. Treating cardiologists and general physicians (for Italy) may also directly contact an eligible candidate, if the patient has no planned routine consultation in the immediate future.

##### Baseline visit

After patients have signed the informed consent form stating their willingness to be randomized, a baseline assessment is planned in the hospital maximum 20 weeks prior to the start of the trial. During this visit, all patients perform a 6MWT, which is in line with the recommendations of the Heart Failure Association of the ESC [5] to evaluate one’s exercise capacity in case cardiopulmonary exercise testing (CPET) is not available.

In addition, every participant receives a self-administered questionnaire package which is filled in during the baseline assessment. These questionnaires have previously been described in the study outcome measures section and details are listed in Table 1*.*

**Table 1 Tab1:** Overview of the questionnaire package

Questionnaire	Description	Number of items	Subscales
Self – care of Heart Failure Index [20]	Self-care	22	Self-care behavior, self-care management, self-care confidence, and symptom perception
Minnesota Living with Heart Failure Questionnaire [21]	Health – related quality of life	21	Physical, socio-economic, and emotional/psychological aspects
Brief Illness Perception Questionnaire [24]	Illness perception	9	Cognitive representation, emotional representation, illness comprehensibility, and perceived cause of illness
Sexual Adjustment Scale [22] (subscale of the Psychosocial Adjustment Scale)	Sexual activity	6	Relationship and sexuality
Needs for Sexual Counseling Scale in Chronic Heart Failure [23]	Sexual activity	21	Symptoms, medication and information, relaxation, relationship, and psychological factors
State Trait Anxiety Inventory [26]	Anxiety	40	State anxiety scale (s-anxiety) and trait anxiety scale (t-anxiety)
Beck Depression Inventory II [27]	Depression	21	Depression and anxiety
Unified theory of acceptance and use of technology questionnaire [28]	User expectations and user experience	37	/
Self – composed questionnaire on nutritional behavior	Nutritional behavior	24	Drinking behavior and eating behavior
Self – composed questionnaire on nutritional knowledge	Nutritional knowledge	12 (14: patients with diabetes)	Knowledge about heart failure (and diabetes) nutrition

Following this assessment, patients are randomized to the intervention or control group according to a sealed randomization scheme with two balanced series of 60 envelopes (one for each country), each containing a random series of 20 control and 40 experimental numbers. In order to handle potential early drop-out of patients, a separate series of 24 sealed and balanced envelopes (12 for each country) is prepared.

Parallel to the baseline assessment, the following parameters are retrieved from the medical patient file as an additional base for providing personalized lifestyle advice: demographic and clinical characteristics, HF-related characteristics and laboratory parameters, risk factors, comorbidities, medication use and exercise capacity.

##### Intervention

Instructions concerning the HeartMan intervention tool are given to the intervention group during a home visit.

### Intervention equipment

Participants randomized to the intervention group are equipped with a multi-monitoring health platform able to monitor, process and fuse physio-psychological and behavioural data. The main component of the trial equipment is the HeartMan wristband sensor developed by BITTIUM (Oulo, Finland). This is an ambulatory recorder and transmitter for heart rate, heart rate variability, galvanic skin response, skin temperature, respiration rate and motion. This wristband has Bluetooth communication, recording function, display, haptic interface and the ability to synchronize with other external devices. Apart from the HeartMan wristband sensor, the equipment consists of registered and commercially available devices including a digital bathroom scale (ADE, Model Silje BE1303), upper arm blood pressure monitor (A&D Medical, Model Number UA-611) and a pill box organizer (PuTwo, 7-Day AM/PM Night Reminder Medi-Planner). Furthermore, a smartphone (Nokia 6 TA_1021) with HeartMan app installed is provided for the duration of the trial.

### Intervention components for the patient

Information coming from the trial equipment, baseline visit and medical patient file are integrated into the HeartMan DSS. The major component is personalized lifestyle advice on nutrition and exercise. The second intervention modality includes general notifications for medication intake with possibility to track the weekly consumption. The third component encompasses cognitive behavioural therapy and mindfulness exercises, which are offered for treating anxiety and depressive symptoms and to improve adherence. The fourth modality are reminders for physician’s appointments, which can additionally be activated upon the patient’s request. The fifth intervention element is a graphical presentation of progress and success in following the advice, designed to improve the patient’s adherence to HF management. The last type of intervention component is education about HF disease and its treatment, which is provided in a library to be consulted on a voluntary basis. All these different types of interventions are delivered by notifications in a personalized way adapted to the patient’s psychological profile (based on State Trait Anxiety Inventory [26] and Beck Depression Inventory II [27]).

A detailed overview of these intervention components is given in Table 2.

**Table 2 Tab2:** Overview of the HeartMan intervention components

Intervention component	Strategy	Description of the intervention
Nutrition	Education on: - knowledge of healthy nutrition - eating behavior	*-* Questionnaire to evaluate knowledge and healthy behavior ○ Baseline and end of the trial *-* Personalized feedback and education is coupled to the questionnaire *-* Possibility to consult questionnaire and education material via the application on a voluntary basis during the trial
Exercise	Endurance exercise	*-* Assessment of physical capacity: cyclo-ergometry (if available) and 6MWT *-* Differentiation based on baseline physical capacity level (low level: cyclo-ergometry < 1 W/kg or 6MWT < 300 m vs. normal level: ≥1 W/kg or 6MWT ≥300 m) *-* Individual exercise program via the application: ○ Frequency: 2–5 times per week ○ Intensity: HR rest + 40–70% HRR or RPE 10–14/20 ○ Time: 10-40 min ○ Type: cycling, walking, steps *-* Individual progress: ○ Increase in frequency or time after a predefined number of weeks (after patient’s approval) ○ Increase in intensity if following criteria are met: • Adherence to exercise therapy > 60% of training sessions • Not overshooting the target heart rate in 80% of the training sessions • Patient’s subjective opinion of exercise intensity: ‘no discomfort’ in 80% of the training sessions • After at least 8 weeks of exercise training
	Resistance exercise	*-* Differentiation based on baseline physical capacity level *-* Individual exercise program via the application: ○ Frequency: 2–3 times per week ○ Intensity: 60–70% 1Repetition maximum ○ Time: 1–2 sets per day ○ Type: dynamic upper and lower limb exercises, with no or light weights *-* Individual progress: ○ Increase in frequency or time after a predefined number of weeks (after patient’s approval) ○ Increase in intensity (from no weights to light weights) after a predefined number of weeks (after patient’s approval)
Medication intake	Weekly pill organizer	*-* Passive pill dispenser, with personalized reminder function in HeartMan application: ○ Guidance to prepare medication once per week ○ Daily personalized notifications to remind the patient to take his medication at the right time *-* Assessment of medication adherence by a weekly question whether the patient has taken the recommended medication or not
Appointments		*-* Personalized reminder function in HeartMan application 1 day before the appointment (only upon the patient’s request)
Mental support	Cognitive behavioral therapy	*-* Patient profiling: adaption of the communication according to the psychological profile (anxious, depressed or low motivation) in order to increase adherence to lifestyle interventions
	Mindfulness exercises	*-* Mindfulness exercises are offered to the patient on a daily basis, adapted to the patient’s profile (anxious, depressed or motivated). *-* Different types of exercises: ○ Listening ○ Focusing ○ Awareness ○ Games
Disease education (illness perception)	Education on: *-* Heart failure disease: causes, symptoms *-* Pharmacological treatment: indications, common side effects *-* Sexual dysfunction and sexual activity	*-* Written education in a depository *-* To consult on a voluntary basis

6MWT, six-minute walking test; HR, heart rate; HRR, heart rate reserve; RPE, rating of perceived exertion

### Intervention component for the caregiver: Web interface

Apart from functionalities focusing on patient’s disease management, HeartMan provides valuable information for formal caregivers. Through a web interface, treating physicians may check adherence and progress of their patient by graphical presentations giving an overview of a certain period of time.

### Alert notifications

Once a patient has received the trial equipment and necessary instructions, the HeartMan app is intended as a stand-alone application used by the patient, without additional support of the HF nurse. Since HF patients need to monitor their weight, heart rate and blood pressure on a regular basis, the HeartMan app will remind them to take these measurements. Unexpected results in these parameters are not transferred to the hospital but the patient will get a notification to contact his treating physician. If predefined exercise requirements concerning heart rate or blood pressure are not met before starting the exercise program or exceed the predefined limits during exercise, a similar notification will appear. A helpdesk for technical questions related to the HeartMan system is available on weekdays from 9 a.m. until 4 p.m. This may strengthen the patient’s role in his own disease management. Table 3 presents the cut-off limits of the alert notifications.

**Table 3 Tab3:** Alert notifications

Parameter	Device	Frequency, time	Alert notification
Weight	Scale	*- weekly measures at rest* • daily or twice a week (configurable by physician) • before breakfast	≥2 kg weight gain in 3 (or less) days
Systolic BP	BP monitor	*- weekly measures at rest* • twice a week • after breakfast and 10 min of resting *- pre-exercise requirement*	> 180 or < 90 mmHg > 180 or < 90 mmHg
Diastolic BP	BP monitor	*- weekly measures at rest* • twice a week • after breakfast and 10 min of resting	> 100 or < 55 mmHg
Heart rate	HeartMan wristband	*- weekly measures at rest* • twice a week • after breakfast and 10 min of resting *- pre-exercise requirement*	> 120 or < 40 bpm > 120 or < 40 bpm
Respiratory rate	HeartMan wristband	*- weekly measures at rest* • twice a week • after breakfast and 10 min of resting	> 24 or < 10 breaths per min

*BP* blood pressure, *bpm* beats per minute

#### Standard care

The HeartMan intervention is provided on top of standard care which is given to all HF patients, regardless of the randomization process. Standard care consists of optimal medical treatment according to the guidelines [3], and written and oral education on HF disease and its management provided by the HF nurse. Regular visits to the treating physician are scheduled several times per year.

#### End-of-study visit

The intervention is terminated after using the system for three to six months. At this time, all participants from the intervention and control group undergo the end-of-study examination in the hospital that entails the same questionnaires and tests as during the baseline visit.

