**Methods:**

HeartMan is a randomized controlled 1:2 (control:intervention) proof-of-concept trial, which will enrol 120 stable ambulatory HF patients with reduced ejection fraction across two European countries. Participants in the intervention group are equipped with a multi-monitoring health platform with the HeartMan wristband sensor as the main component. HeartMan provides guidance through a decision support system on four domains of disease management (exercise, nutrition, medication adherence and mental support), adapted to the patient’s medical and psychological profile. The primary endpoint of the study is improvement in self-care and HRQoL after a six-months intervention. Secondary endpoints are the effects of HeartMan on: behavioural outcomes, illness perception, clinical outcomes and mental state.

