## Study design

### Design

HeartMan is a randomized controlled 1:2 (control:intervention) proof-of-concept trial, being conducted across two countries (Belgium and Italy) to compare standard care in HF with the addition of a personal mHealth system on top of standard care. In each country 60 patients are enrolled for a six-month period. Hence 40 patients in total are included in the control group and 80 in the intervention group.

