### Study objectives and outcome measures

The overall objective of HeartMan is to improve disease management, resulting in an improvement in HRQoL after a 6 months intervention period.

Secondary objectives are the effects of HeartMan on behavioural outcomes, illness perception and clinical outcomes which may impact disease management and HRQoL. Additional secondary aims encompass the effects of psychological interventions within HeartMan and a user-friendly design of the HeartMan system.

Primary and secondary outcome measures, which are assessed in the intervention and control group, are listed below. These measures are collected at start and end of the study, unless otherwise stated.

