#### Primary objective

The primary endpoint is the self-reported improvement in self-care and HRQoL, measured by the Self-care of Heart Failure Index [20] and Minnesota Living with Heart Failure Questionnaire [21]

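### The primary endpoint is set at six months, but the only outcome visit may fall anywhere from three to six months after system start

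*Protocol article*

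**What the plan says.** Three places in the protocol article give six months:

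- Abstract, Methods: "The primary endpoint of the study is improvement in self-care and HRQoL after a six-months intervention".
- Design: "In each country 60 patients are enrolled for a six-month period".
- Study objectives and outcome measures: the overall objective is better disease management, "resulting in an improvement in HRQoL after a 6 months intervention period".

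The End-of-study visit section gives a range: "The intervention is terminated after using the system for three to six months". It continues: "At this time, all participants from the intervention and control group undergo the end-of-study examination in the hospital", with the same questionnaires and tests as at baseline.

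The timing of the outcome data depends on that visit. Under Study objectives and outcome measures, the general rule is: "These measures are collected at start and end of the study, unless otherwise stated". The Primary objective section reads "The primary endpoint is the self-reported improvement in self-care and HRQoL, measured by the Self-care of Heart Failure Index" and adds the Minnesota questionnaire. It gives no month and no further measurement time. The Statistical analysis section compares baseline with end-of-study data through a repeated-measures model with a group-by-time interaction, and it also fixes no month.

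**The concern.** The article states two durations for one endpoint. Three to six months is not a window around six months. Six is its upper limit and half of six its lower limit, so every departure is towards shorter exposure. No rule says who stops when. Each patient has only one post-baseline value on the primary questionnaires, so an early end visit replaces the six-month measurement and does not add to it. At stake is what the primary estimate refers to: a six-month effect, as the abstract and objective say, or an average over durations that the plan does not control.

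**Working it through.** No figure in the plan needs reproducing here. The check compares the texts, with simple arithmetic on durations.

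**Step 1, durations in weeks.** Inputs: three and six months (End-of-study visit); six months (Abstract, Design, Study objectives and outcome measures). Conversion: weeks = months × 52/12.

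- 3 × 52/12 = 13 weeks
- 6 × 52/12 = 26 weeks
- Largest shortfall: 26 − 13 = 13 weeks, and 13/26 = 50%

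The 50% is the extreme case. The article gives no distribution of durations, so the average shortfall is unknown and lies between 0 and 13 weeks.

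**Step 2, is there another six-month measurement?** The general rule is collection at start and end. No exception is stated for the two primary questionnaires, and no separate six-month visit is described. A patient whose end visit is at month 3 therefore has no observed month-6 value.

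**Step 3, what the interaction term estimates.** With two time points, the group-by-time term is the difference between arms in mean change from baseline to the end visit. Let Δ(t) be the true difference between arms after t weeks. If end visits fall at times t between 13 and 26 weeks, with the same distribution in both arms, the term targets the average of Δ(t) over that distribution. This equals Δ(26) if every visit is at week 26, or if Δ(t) is flat from week 13 on. The plan as written ensures neither, and the article does not say how the effect develops over time.

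**Step 4, from which date six months should be counted.** The Baseline visit section lets the baseline assessment take place up to 20 weeks before the trial starts, and randomization follows that assessment. If randomization comes directly after baseline (an assumption), a visit 26 weeks after randomization could leave as little as 26 − 20 = 6 weeks of system use. Counting from the intervention start avoids this.

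**The case against.** **Six months may be a nominal or maximum duration.** That is a fair reading of intent, but a patient measured at month 3 has still not been measured after six months of intervention.

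**The range may be meant for drop-outs.** The section on missing data deals with drop-outs separately. The End-of-study visit section describes the ordinary end of the intervention for everyone.

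**A journal article condenses the full protocol.** Visit windows are often left to the full document, and the flow chart is not shown. Here, however, nothing is merely left out: the article prints two durations that disagree.

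**Several stronger readings are tempting, and the article does not support them.**

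- A reader might infer that the trial could not support its conclusion. The Discussion and the abstract's closing statement name no time point, and neither does the Primary objective section. The mismatch is with the six-month wording of the abstract, design and objective.
- A reader might infer that a six-month effect is lost for good. That holds for an individual's unmeasured value. For the group, a model using recorded visit times could estimate it if enough patients are seen near month 6, and if the assumed time course, and the reasons for early visits, allow it.
- A reader might infer bias between arms, because controls have no system use to count from. The text has both arms examined at the same time, which suggests parallel timing. Nothing says that the arms differ.
- A reader might infer a large loss of dose from the condition for raising endurance intensity, "After at least 8 weeks of exercise training". This leaves at most 13 − 8 = 5 weeks at raised intensity for a three-month patient, against 26 − 8 = 18 weeks for a six-month patient. Both are upper bounds for one progression rule in one of several components, and they do not show that the effect still grows after month 3.
- A reader might infer a loss of power. The sample size rests on heart rate, not on the questionnaires, and the course of the effect is not given, so none can be derived.

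**Conclusion.** The conflict is in the current text and should be fixed. As written, the primary analysis would average over exposures of about 13 to 26 weeks and would not match an endpoint declared at six months. The size is a shortfall of up to 13 weeks (50%) for an individual patient; the average is unknown. The finding assumes that the range applies to ordinary completers, as the section reads, and that no other post-baseline assessment of the primary questionnaires exists. With the parallel timing that the text suggests, the comparison between arms remains fair. What changes is the quantity estimated, and the loss of an observed six-month value for patients seen early.

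**What to change.** In the End-of-study visit section, replace the range with one outcome visit six months after the scheduled intervention start. Give it a narrow window (for example 26 weeks plus or minus 2 weeks; the 2 weeks is a suggestion). It should apply to every patient in both arms, however long the system was used. Controls should be counted from the start date they would have had, not from randomization.

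If six months is not feasible for all, restate the duration as three to six months in the Abstract, Design, and Study objectives and outcome measures sections. In either case, record and report each patient's actual assessment time.

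The preferred route costs a protocol amendment, rescheduled visits and up to about 13 more weeks of device use for some patients, in a trial already enrolling. Patients already examined early cannot be corrected. The fallback needs only text changes, at the price of a less specific endpoint time. Neither route removes the variable gap before the start: with baseline up to 20 weeks earlier, the interval from baseline to a 26-week visit can still reach 20 + 26 = 46 weeks.
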